## Abstract

**Background:**

Uncertainty is integral to evidence-informed decision making and is of particular importance for preference-sensitive decisions. Communicating uncertainty to patients and the public has long been identified as a goal in the informed and shared decision-making movement. Despite this, there is little quantitative research on how uncertainty in health information is perceived by readers.

**Objective:**

The objective of this study is to design an experiment to examine how different degrees of uncertainty (Q1) and different types of uncertainty (Q2) impact patients’ perception of treatment effectiveness, the body of evidence, text quality, and hypothetical treatment intention. The experiment also examines whether there is an additive effect when multiple sources of uncertainty are communicated (Q3).

**Methods:**

We developed 8 variations of a research summary set in a hypothetical scenario for a treatment decision in the context of tinnitus. These were modified only in the degree of uncertainty relating to the evidence of the presented treatment. We recruited members of the German public from a Web-based research panel and randomized them to one of 8 variations of the research summary to examine the 3 research questions. The trial was only open to the members of the research panel. The outcomes are perception of the effectiveness of the treatment (primary), certainty in the judgement of treatment effectiveness, perception of the body of evidence relating to the treatment, text quality, and decisional intention (secondary). Outcomes were self-assessed. We aimed to recruit 1500 participants to the trial. The recruitment and data collection was fully automated. Ethical approval was waivered by an ethics committee because of the negligible risk to participants.

**Results:**

This protocol is retrospectively published in its original format. In the meantime, the trial was set up and the data collection was completed. Data collection was conducted in May 2018. A total of 1727 eligible panel members were enrolled.

**Conclusions:**

We aim to publish the results in a peer-reviewed journal by the end of 2019. In addition, results will be presented at conferences and disseminated among developers of guidance for the development of evidence-based health information and decision aids.

**Trial Registration:**

German Clinical Trials Register DRKS00015911; https://www.drks.de/drks_web/navigate.do? navigationId=trial.HTML&TRIAL_ID=DRKS00015911 (Archived by WebCite at http://www.webcitation.org/77zyZTGzk)

**International Registered Report Identifier (IRRID):**

DERR1-10.2196/13425

## Introduction

### Background

Uncertainty pervades health care and is integral to evidence-informed decision making. The many layers of uncertainty, however, have hampered a common understanding of the subject. Han et al have developed a helpful taxonomy by identifying various types of uncertainty and classifying them into 3 dimensions [1]:

Sources of uncertainty: These include, for example, ambiguity arising from conflicting evidence or statistical uncertainty.Issues arising from uncertainty: These include difficulties in decision making resulting from scientific uncertainty, for example, regarding treatment effects.Their loci, that is, uncertainty may exist in the mind of the patient, the health care provider, or both.

In terms of these dimensions, our experiment examines how communication of scientific uncertainty affects the perception of treatment effectiveness by patients and the public. Helping patients and consumers to understand and deal with uncertainty has been identified as one of the goals of the shared decision making and informed choices movement [2]. Understanding uncertainty is of particular importance for preference-sensitive decisions, that is, when there is a close trade-off between benefits and harms, and patient values and preferences are highly variable. Communicating uncertainty, however, poses many difficulties. Often information providers have to decide which of the many sources of uncertainty are most relevant to patients. Selection is required to prevent information overload, which can prompt people to base their decisions on heuristics rather than evidence [3]. Furthermore, communication of uncertainty may also have detrimental effects, for example, by hampering understanding or decreasing the credibility of the information provider [4,5].

Research on how to communicate uncertainty regarding the benefits and harms of treatments to patients and the public is limited. A systematic review by the Agency for Healthcare Research and Quality identified 8 controlled studies with 9 comparisons, including 6 randomized trials [6]. Of these studies, 4 examined statistical uncertainty, 4 studied different ways of communicating net benefit, and 1 addressed uncertainty arising from the use of a surrogate outcome. These studies were very heterogeneous in terms of context (including cancer screening and treatment decision making), interventions (including written information, drug fact boxes, and multifaceted interventions), and outcomes (including risk perception and decision making).

### Objectives

We are not aware of any studies investigating whether perceptions of uncertainty depend on the degree, type, or amount of uncertainty presented in written health information. Thus, we decided to address the following 3 questions in our study:

Degree of uncertainty: Do members of the public perceive treatment effects differently depending on the choice of words used to express the certainty of those treatment effects?Type of uncertainty: Do members of the public interpret uncertain treatment effects differently depending on the type of uncertainty?Number of sources of uncertainty: Is there an additive effect of multiple sources of uncertainty?

We investigated these questions using 8 variations of a written piece of hypothetical consumer health information (research summary) set in a treatment decision scenario in the context of tinnitus. The research summaries were presented to a broad group of members of the German public using a Web-based research panel. Although the study was conducted with Web-based health information, we believe the results will be applicable to all types of written health information, including printed material.

We designed the experiment as a Web-based randomized superiority study, with 8 parallel groups allocated in an equal ratio (between-group design).

## Methods

### Procedures

We recruited members of the public from a Web-based research panel. Panel members had to be at least aged 18 years and able to read and write German. No other inclusion restrictions were applied.

The participants were first provided with a short introduction to the study and an informed consent sheet. We then collected information on age, sex, and educational degree. Participants were then asked to imagine having tinnitus and having unsuccessfully tried several treatments (see Multimedia Appendix 1). They were then randomly presented with one version of different variations of the research summary on the internet. These contained information on the medical condition and a short summary of evidence for a fictitious new tinnitus medication called *Oroxil* (see Multimedia Appendix 1). After presenting participants with the research summaries, we collected data on different outcomes using a questionnaire developed for the purpose of this study. We asked participants to return to the research summary as needed while answering the questions. At the end of the experiment, participants were asked about their profession (medical or nonmedical) and their history of tinnitus (present or not present). Participants were neither aware of the specific research questions nor of the alternative presentations. The original research summaries were written in German and translated into English for this publication.

### Interventions

We chose a treatment scenario in the context of tinnitus and developed 8 variations of the research summary based on our experience and use of language in providing evidence-based health information to consumers through Germany’s statutory health website [7]. In accordance with the objectives of our study, we altered the research summary regarding the degree of uncertainty, the sources of uncertainty, and the number of sources of uncertainty. This resulted in 8 variations, two of which were used in 2 (statistically independent) comparisons (Table 1). An exemplary version of the research summary is provided in the Multimedia Appendix 1.

For the first objective of the study (Q1), we formulated 3 versions of the research summary with different degrees of uncertainty of the treatment effect. One version (A) describes a certain treatment effect and the other (B), a possible, but not certain treatment effect (indication of effect). The third version (B1) is identical to variation B but includes an additional statement on the need for further research. The semantic variations in the degrees of uncertainty of the treatment effect were based on the methods for the assessment of treatment benefits developed by the German Institute for Quality and Efficiency in Health Care (IQWiG) [8].

For the second objective (Q2), we drew on the GRADE (Grading of Recommendations Assessment, Development and Evaluation) framework to categorize different types of uncertainty. According to GRADE, uncertainty can arise from risk of bias, (unexplained) inconsistency, indirectness, imprecision, and other threats to validity, such as publication bias or vested interests [9]. We therefore formulated 3 additional variations of the research summary describing publication bias and vested interests (B2), indirectness (B3), and imprecision (B4). We will also include variation B1 in this comparison.

For the third objective of the study (Q3), we developed 2 further variations that contained a combination of 2 or 3 sources of uncertainty (B42 and B432). A variation including only 1 source of uncertainty (B4) is included in this comparison.

**Table 1 table1:** Variations of the research summary used to examine the 3 overarching research questions (translated from German).

Variations for research objective and identifier		Version	Variation in text

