### Outcomes

Our primary outcome is the perception of treatment effectiveness. The secondary outcomes are subjective certainty in the judgement of treatment effectiveness, perception of the body of evidence, hypothetical treatment intention, and perception of text quality.

The perception of treatment effectiveness was measured with 1 item on an ordinal scale (*How do you judge the effectiveness of Oroxil?*) with 5 possible answers: (a) It is proven that Oroxil can help; (b) Oroxil may possibly help; (c) It is unclear, whether Oroxil helps; (d) Oroxil may not help; and (e) Oroxil definitely does not help.

Subjective certainty in the judgement of treatment effectiveness was measured on a 5-point Likert scale, ranging from *not certain at all* to *very certain*. As this relates to the first question on perceptions of treatment effectiveness, data on this item were gathered immediately after answering the first question.

The perception of the body of evidence was measured with a 6-item semantic differential (Cronbach alpha=.81), with each item measured on a 5-point Likert scale. Participants were asked to rate the body of evidence as follows:

Certain to uncertainReliable to unreliableValid to not validGeneralizable to not generalizableExcellent to poorTrustworthy to untrustworthy

The hypothetical treatment intention was measured using 1 item (*How would you decide?*) measured on a 5-point Likert scale with 2 poles: (a) definitely not take Oroxil and (b) definitely take Oroxil.

The perception of text quality was measured with a 9-item semantic differential (Cronbach alpha=.81) based on previous literature [10,11]. The construct included the following items measured on a 5-point Likert scale:

Interesting to uninterestingBalanced to 1-sidedComprehensible to incomprehensibleCredible to incredibleClear to unclearWell done to not well doneProfessional to unprofessionalAppealing to not appealingRespectable to not respectable

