### Statistical Analysis

We will present demographic characteristics of the sample using frequencies, in case of categorical data, and measures of location (mean and median) and variation (SD, interquartile ranges [IQRs], and ranges), in case of continuous data.

We will treat the primary outcome variable as an ordinal scale with 5 possible values, where higher values indicate an increase in the perception of effectiveness (5=it has been proven that the treatment can help to 1=treatment definitely cannot help). We will present data as medians, IQRs, and ranges for each group. We will also present means and SDs, as well as the proportions for each possible answer in descriptive tables. This will also help to establish the practical relevance of the results.

For the secondary outcomes *perception of the body of evidence* and *text quality*, we will combine the items of each of the scales into 1 index by averaging their values, where a higher value will indicate better perception of the body of evidence or text quality.

For our confirmatory statistical analyses of the primary and secondary outcomes, we will conduct Kruskall-Wallis tests to test for overall differences between the groups within each of our 3 primary study questions. We chose to use a nonparametric test to account for the types of scales used (ordinal scaling or unequal differences between items).

In case of statistical significance, we will conduct a multiple testing procedure to perform pairwise comparisons within the groups by means of the Dwass-Steel-Critchlow-Fligner multiple comparison analysis, which is based on pairwise 2-sample Wilcoxon comparisons. All comparisons between groups across the 3 overarching study questions will be considered explorative (eg, A vs B432).

We will conduct sensitivity analyses by means of an analysis of variance (ANOVA) to test for the overall differences between the groups within each of our 3 overarching study questions. In case of statistical significance, we will conduct pairwise comparisons by means of Tukey honestly significant difference procedure. We will inspect data to ensure that they meet distributional assumptions (normality and equal variance) before applying statistical tests.

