Statistical analyses will be conducted in SAS version 9.4 (SAS Institute Inc). All statistical tests will be 2-sided and performed using a 5% significance level. Where applicable, differences in means between groups will be presented together with a 95% CI. All analyses will be conducted on an intention-to-treat basis. Explorative analyses based on potential moderators and mediators are not predetermined.

As we will collect outcome data immediately after the presentation of the research summaries and panel members need to finish the questionnaire to receive an incentive, we have no major concerns regarding missing data. Furthermore, we assume that any dropouts will be likely to be missing at random, as we believe it is unlikely that the intervention has an influence on the responses to the questionnaire. Thus, we do not plan to employ any imputation methods. In case of missing data, we will present this information descriptively.

As the experiment is Web-based and participants come from a panel that provides incentives for participation, there is a risk that some participants only participate to collect their incentive and do not provide valid answers. As a measure of quality assurance, we will exclude data from participants who answer all questions in less than 2 min, spend less than 20 seconds on the page displaying the research summary, and spend less than 1.5 min between reading the research summary and completing the questionnaire (so called speeders). These time limits were determined by a priori test readings. We will also exclude participants who provide all answers in the same column for the matrix questions, that is, when more than 1 item is displayed on the screen (so called straightliners).

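### Comparisons that share an arm are wrongly called statistically independent, and all five outcomes are labelled confirmatory at 5% each with no error control across outcomes

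*Protocol article*

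**What the plan says.** **Shared arms.** Under Interventions, the protocol article describes the reuse of two versions: "This resulted in 8 variations, two of which were used in 2 (statistically independent) comparisons (Table 1". The same section shows the overlap. Of B1 it says, for the question on type of uncertainty, "We will also include variation B1 in this comparison". For the question on number of sources, "A variation including only 1 source of uncertainty (B4) is included in this comparison". Table 1 agrees: Q1 compares A, B and B1; Q2 compares B1, B2, B3 and B4; Q3 compares B4, B42 and B432. The design is between-group with eight parallel arms, so each arm is one set of people.

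**Outcomes and tests.** Under Outcomes, "Our primary outcome is the perception of treatment effectiveness", and four secondary outcomes follow: "subjective certainty in the judgement of treatment effectiveness, perception of the body of evidence, hypothetical treatment intention, and perception of text quality". Statistical Analysis then announces Kruskal-Wallis tests within each of the three questions, introduced by "For our confirmatory statistical analyses of the primary and secondary outcomes". The level is fixed for all of them: "All statistical tests will be 2-sided and performed using a 5% significance level".

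**Error control.** The only multiplicity step is the Dwass-Steel-Critchlow-Fligner procedure for pairs, after a significant overall test within one question. Pairs that cross questions are explorative. The Sample Size Calculation section attaches the confirmatory label to the primary outcome and to no other.

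**The concern.** There are two separate problems.

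First, two tests that use the same participants' answers in a common arm cannot be independent. An unusual B1 sample can make both the degree and the type question significant, and an unusual B4 sample can do the same for type and number of sources. A reader told that these comparisons are independent would count one chance event as two pieces of evidence.

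Second, a confirmatory label tells readers that the risk of a false claim is controlled. Here it is controlled only for pairs within one question and one outcome. Nothing orders, gates or splits the 5% across the five outcomes of a question. The label on the secondary outcomes also does not fit the Sample Size Calculation section, which treats the primary outcome as the confirmatory one.

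**Working it through.** **1. The plan's own figure.** For a four-group one-way ANOVA with F = 0.15, two-sided 5% and n per group, power comes from the noncentral F distribution with noncentrality N × F². At n = 159, N = 4 × 159 = 636 and 636 × 0.0225 = 14.31; power is 0.901. At n = 158 it is 0.899. So 159 per group is reproduced. Adding 15%: 159 × 1.15 = 182.85, so 183 per group and 8 × 183 = 1464, within the planned 1500. The sample size is correct for one test at an unadjusted 5%.

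**2. Dependence from a shared arm.** With equal n and common variance s², the covariance of (A − B1) and (B1 − B2) is −s²/n, and each difference has variance 2s²/n. The correlation is −0.5, not 0.

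For the Kruskal-Wallis tests themselves, a simulation used 8 arms of 187, a five-category outcome (assumed distribution), no true differences and the overlap in Table 1, with 6000 replicates of five uncorrelated outcomes:

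| Pair of questions | Shared arm | Correlation of statistics | P(second significant given first) |
|---|---|---|---|
| Q1, Q2 | B1 | 0.21 | 14.5% |
| Q2, Q3 | B4 | 0.21 | 15.1% |
| Q1, Q3 | none | about 0 | 4.3% (5% expected) |

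Other runs, with other assumed distributions and seeds, put the arm-sharing figure between 14% and 17%; about 15% is a fair summary. The chance that both tests of such a pair are falsely significant is then about 0.05 × 0.15 = 0.75%, against 0.05 × 0.05 = 0.25% under independence.

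**3. Familywise error, three primary-outcome tests.**
- If independent: 1 − 0.95³ = 14.3%.
- With the shared arms, by inclusion and exclusion: 3 × 0.05 − (0.0075 + 0.0075 + 0.0025) = 13.25%, plus the chance that all three are significant. That chance is at most 0.25% (the joint chance for Q1 and Q3), so the result lies between 13.25% and 13.5%.
- Simulation: about 13% to 13.7%.

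The overlap lowers this rate slightly.

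**4. Familywise error, all confirmatory tests.** The count is 3 questions × (1 + 4) outcomes = 15.
- If all were independent: 1 − 0.95¹⁵ = 53.7%.
- Simulated with shared arms, by assumed correlation between outcomes (the documents give none):

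| Correlation between outcomes | At least one false positive in 15 |
|---|---|
| 0 | 50% |
| 0.3 | 48% |
| 0.5 | 45% |
| 0.7 | 39% |

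Within one question alone, five tests give 1 − 0.95⁵ = 22.6% if the outcomes were independent, and less if they are correlated.

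**5. Power if alpha is also adjusted across questions.** Effective n per group after removing the 15% allowance is 1500 / 8 / 1.15 = 163. Holm's first step for three tests uses 0.05 / 3 = 1.67%. At F = 0.15:

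| Comparison | Power at 5% | Power at 1.67% |
|---|---|---|
| Three groups (Q1, Q3) | 85% | 73% |
| Four groups (Q2) | 91% | 82% |

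With the 1727 randomized, before the planned exclusions of speeders and straightliners, the effective n is about 187. Power falls from 90% to 80% (three groups) and from 94% to 88% (four groups).

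**The case against.** The strongest reply is that degree, type and number of sources are three distinct questions. Each has one primary outcome and its own pairwise procedure, and the article never says that one positive question makes the study a success. Three separate families at 5% are then defensible. That stands, with two limits. The article does not make the argument, and its independence claim cannot stand in for it. Nor would it cover the four secondary outcomes in each question that are called confirmatory at the full 5%.

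It can also be said that the label on the secondary outcomes is a drafting slip, since the sample size section reserves it for the primary outcome. That is plausible, and it is a reason to correct the text. It does not make the two sections agree. A statistical analysis plan that is not shown cannot settle this either: the label, the level and the independence claim are all stated in the article.

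Three stronger readings do not hold. A reader might infer that the shared arms inflate the familywise error; the calculation shows a small decrease. A reader might infer that adjustment across the three questions is required; nothing in the article commits to a single study-wide claim. And a reader might infer that the sample size is wrong or the individual tests invalid; 159 per group is reproduced, and each test keeps its 5% level.

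**Conclusion.** The independence statement is false for Q1 with Q2 and for Q2 with Q3. It is right only for Q1 with Q3, which share no arm. The consequence is for interpretation: the conditional chance of a second false positive is about 15% instead of 5%, while the error over the three primary tests stays at about 13.5% against 14.3%.

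The weightier problem is the confirmatory label on 15 tests with no control across outcomes. The chance of at least one false confirmatory claim is roughly 40 to 50%. This assumes no true difference anywhere, near-equal arms of 187, and between-outcome correlations from 0 to 0.7. It gives all 15 tests equal weight, although the article ranks one outcome as primary. The plan should be corrected on both points; the primary tests themselves remain usable.

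**What to change.** 1. Under Interventions, delete the claim of statistical independence. State that Q1 and Q2 share B1 and that Q2 and Q3 share B4, so significant answers to two arm-sharing questions are not independent confirmations.
2. Reserve the confirmatory label for the primary-outcome test of each question, in line with the sample size section.
3. Within each question, test the secondary outcomes confirmatorily only after its primary test is significant, in a fixed stated order, stopping at the first that is not. Otherwise call them explorative.
4. Across questions, either state that they are three separate families, each at 5%, with the reason, or choose Holm. If Holm is chosen and the secondary outcomes are to be covered too, say how alpha is passed on: the same share cannot be spent both on another question and on secondary outcomes.

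**Cost.** Items 1 to 3 are wording and cost the primary tests no power. Holm is optional. Its first step takes power at F = 0.15 from about 85% to 73% (three groups) and from 91% to 82% (four groups) at 1500. The sample can no longer be enlarged.

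Data collection ended in May 2018, so any such change should be dated and reported as made after data collection.
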